**Methods/design:**

Four-arm randomised controlled trial. The study tests two types of intervention that are intended to increase physical activity among currently inactive 18- to 74-year-old people with hypertension or high-normal blood pressure. This study will assess the effectiveness of a 12-week sports-oriented exercise programme, the efficacy of a web-delivered self-help tool to promote and support sports participation and healthy behaviour change and the effect of these interventions in combination. The control arm will be a standard care general practitioner referral for gym-based exercise. Participants will be allocated using block randomisation. The first author and primary analyst is blinded to participant allocation. The primary outcome measures will be time spent in physical activity assessed in metabolic equivalent minutes per week using the International Physical Activity Questionnaire 1 year after commencement of the intervention. Secondary outcomes include increased involvement in sporting activity and biomedical health outcomes including change in body mass index, and waist and hip measurement and reductions in blood pressure.

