#### Research questions and hypotheses

The primary purpose of the trial is to test the independent and synergistic efficacy of the 12-week sports-oriented exercise referral intervention and the self-help web-based intervention intended to promote sustained and increased levels of physical activity over a period of 12 months. Do these interventions separately and in combination improve these indicators and do they improve them above that expected by existing gym-based GP referral alone? The secondary questions are whether these interventions improve other clinical indicators of cardiovascular health (for example, body mass index, waist and hip measures, blood pressure and other measures that contribute to the QRisk2 risk indicator) above that expected by existing gym-based GP referral? Do these interventions increase participation in sporting activity over a period of 12 months?

The interventions individually will be regarded as successful if they lead to an average increase in activity of 100 metabolic equivalent of task (MET)-minutes per week. This equates to engaging in an extra moderate intensity activity, say brisk walking (3.3 MET) for 30 minutes per week. The new interventions will be regarded as superior to the standard gym-based referral if they increase activity levels above those of the standard care gym-based exercise by 20 MET-minutes per week.

We will assess changes in indicators relating to cardiovascular health including blood pressure, weight, and waist and hip circumference. In terms of blood pressure, the interventions will be regarded as successful if they lead to an average decrease in blood pressure of 2.5 mmHg. We will assess the proportion of the sample reducing their blood pressure by more than 10 mmHg and an intervention will be regarded as a success if more than 20% of the members of that study arm achieve a reduction greater than this. The interventions will also be deemed to have been successful in promoting sports participation if they increase sports-related activity by 100 MET-minutes per week.

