### Sample size and power calculations and randomisation

Davies and colleagues report a meta-analysis of internet-based exercise intervention studies which suggests an average effect size of d = 0.14
[16]. A Cochrane review of general interventions to promote activity among inactive adults reports an average SMD = 0.28, but notes considerable heterogeneity in effects sizes
[4]. In the case of internet interventions aimed at reducing blood pressure, effects sizes of the order of SMD = 0.27 and 0.17 for systolic and diastolic blood pressure, respectively (equating to drops of 3.8 and 2.1 mmHg, respectively), have been identified in a recent meta-analysis
[35]. Based on these analyses, an effect size of 0.125 can be assumed for comparing means of MET-minutes per week and mmHg between the intervention and control arms (equinumerous) for a two-arm study. With this effect size, if each arm consists of 500 subjects, a power of 80% is obtained for a two-sided statistical contrast to show statistical significance, at the 5% level, of the difference of the means of the two arms with respect to these outcome variables. It is therefore decided that there will be 500 subjects in each of the four arms of the present study.

Block randomisation is to be conducted by the University of Surrey’s Clinical Research Centre. Participants cannot be blinded to the nature of the intervention they are receiving and for reasons of monitoring and contacting participants the research assistant also cannot be blinded. The primary analyst will be blinded to participant allocation.

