#### Intervention effectiveness

For the primary outcome of activity, and assuming normal variable distributions, the intervention arms will be compared to the control arm using *t*-tests and one-way analysis of covariance using study arm as the between-subjects factor and baseline activity scores as the covariate (following Senn,
[36]). Similar analyses will be conducted for the secondary outcome variables and in all cases effect sizes reported. Where variable distributions do not initially permit the use of parametric inference tests, variables will be subjected to mathematical transformation to achieve normality. In cases where transformations are not effective, non-parametric tests on difference scores will be used. Differences between arms in the proportions achieving more than 10 mmHg reductions in blood pressure will be assessed using chi-square tests.

Analyses will be conducted on a per-protocol basis. Interim assessment of the efficacy of the interventions will be made at 6 months.

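### Blood pressure has two success rules, neither tied to the comparison with control, and the 20% responder rule can be met by an arm with no benefit

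*Protocol article*

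**What the plan says.** The abstract names one primary outcome: "The primary outcome measures will be time spent in physical activity assessed in metabolic equivalent minutes per week", measured by questionnaire one year after the start. Sport participation, BMI, waist, hip and blood pressure are secondary.

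Under Research questions and hypotheses, some secondary outcomes receive success criteria of their own:

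- Mean blood pressure: "In terms of blood pressure, the interventions will be regarded as successful if they lead to an average decrease in blood pressure of 2.5 mmHg".
- Share of the arm falling by more than 10 mmHg: "an intervention will be regarded as a success if more than 20% of the members of that study arm achieve a reduction greater than this".
- Sport: "The interventions will also be deemed to have been successful in promoting sports participation if they increase sports-related activity by 100 MET-minutes per week".

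For activity, the same section separates success (an average gain of 100 MET-minutes) from superiority to gym referral (20 MET-minutes more than control). Blood pressure and sport get no such second criterion.

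Under Intervention effectiveness, each intervention arm is compared with control by t-test and by analysis of covariance on the baseline score. For the rest, "Similar analyses will be conducted for the secondary outcome variables and in all cases effect sizes reported". Chi-square tests compare the arms on the share falling by more than 10 mmHg.

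The sample size section covers blood pressure as well as activity: "an effect size of 0.125 can be assumed for comparing means of MET-minutes per week and mmHg between the intervention and control arms (equinumerous"), with the result that "It is therefore decided that there will be 500 subjects in each of the four arms of the present study".

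**The concern.** The secondary question on cardiovascular indicators is comparative: do the interventions improve them beyond what gym referral achieves? The success rules do not answer it. The 20% rule is a count within one arm. The 2.5 mmHg rule names no comparator. Neither refers to the tests under Intervention effectiveness, and the text does not say which rule governs when they disagree.

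A within-arm responder count does not isolate an effect. Blood pressure varies between visits, so some people fall by more than 10 mmHg when the group mean has not moved, and any fall shared by all arms adds to them. At stake is a published, prespecified claim of success that the control arm would have earned equally.

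The wording also leaves open what a blood pressure or sport success means if the activity comparison is negative. The mean and sport criteria are limited to their own domain. The 20% sentence carries no such limit of its own.

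**Working it through.** The article gives no operating characteristics for these rules, so there is no stated figure for them to reproduce. The nearest is the power statement, "a power of 80% is obtained for a two-sided statistical contrast to show statistical significance, at the 5% level", for 500 per arm at an effect size of 0.125. Check: 0.125 × √(500/2) = 1.976, and Φ(1.976 − 1.960) = 0.507. That does not reproduce 80%. It is a separate matter, and only the 500 per arm is used below.

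**Inputs**

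- SD of blood pressure, from the sample size section: systolic 3.8/0.27 = 14.1 mmHg; diastolic 2.1/0.17 = 12.4 mmHg.
- n = 500 per arm.
- Baseline-to-follow-up correlation r: not given, so assumed at 0.5 to 0.8.
- Normally distributed changes with true mean change zero: assumed.

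**Formulas**

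- SD of change = SD × √(2(1 − r)).
- Chance that one person falls by more than 10 mmHg: p = 1 − Φ(10/SD of change).
- 20% rule met: more than 100 of 500, binomial with probability p.
- Mean rule met: 1 − Φ(2.5/(SD of change/√500)).

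**Systolic, no true change**

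| r | SD of change (mmHg) | p | 20% rule met | Mean rule met |
|---|---|---|---|---|
| 0.5 | 14.1 | 23.9% | 98% | 0.004% |
| 0.6 | 12.6 | 21.3% | 75% | below 0.001% |
| 0.7 | 10.9 | 17.9% | 11% | below 0.001% |
| 0.8 | 8.9 | 13.1% | 0% | below 0.001% |

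The turning point is p = 20%, where the SD of change is 10/0.842 = 11.9 mmHg. That gives r = 1 − 11.9²/(2 × 14.1²) = 0.64. If the SD behind the cited effect size is itself an SD of change, the first row applies directly.

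The rule does not say which pressure it uses. For diastolic pressure the same steps give 67%, 15%, 0.1% and 0%.

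**A fall shared by all arms.** If every arm, control included, truly falls by 2.5 mmHg, then p = 1 − Φ(7.5/SD of change). On systolic pressure each arm meets the 20% rule with probability of at least 99% for r from 0.5 to 0.7, and about 47% at r = 0.8.

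**Conflict in the other direction.** At a mean fall of exactly 2.5 mmHg, the share above 10 mmHg is 1 − Φ(7.5/8) = 17% if the SD of change is 8 mmHg, and 1 − Φ(7.5/12) = 27% if it is 12 mmHg. With the systolic SD these correspond to r of about 0.84 and 0.64. The first case needs a high correlation, so the likelier conflict is the one in the table: responder rule passed, mean rule failed.

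**The case against.** The strongest case against the point is that it asks a condensed article for what an analysis plan supplies. The outcomes are labelled secondary in the abstract and in the research questions. The mean and sport criteria are confined to their domain, and the 20% sentence sits within the blood pressure discussion. The trial is also sized for mmHg, so a separate blood pressure conclusion was evidently intended.

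Much of that stands. A reader might infer that the fault is unadjusted testing of many secondary outcomes in three arms, so that an ineffective intervention will often be credited with a benefit. The documents do not support that reading. Multiplicity handling for secondary outcomes is commonly left to the analysis plan, which is not shown. The success criteria are thresholds on change with no p-value, so a count of significance tests does not measure them. BMI, waist and hip have no success criterion at all.

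The size of that risk is context only. Take six outcomes (sport, BMI, waist, hip, systolic and diastolic pressure) with assumed between-outcome correlations from 0.7 to 0, each tested at two-sided 5%. Simulation puts the chance of at least one false positive favouring the intervention at about 8–14% for one ineffective arm, and 19–32% if all three are ineffective.

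A reader might also infer that the protocol lets a secondary success replace a failed primary. It does not say so; it leaves the relation unstated.

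The objection does not reach the two published blood pressure rules. An analysis plan that adjusted p-values would leave both in force.

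**Conclusion.** The point holds as a fault in what the protocol article states. Blood pressure has two stand-alone success rules, with no stated order and no link to the planned comparison with control. They can give opposite answers: with no true change, the 20% rule on systolic pressure is met with probability from about 98% down to 0% as r goes from 0.5 to 0.8, while the mean rule is met in about 0.004% of cases or fewer.

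The result depends on r, which the article does not give, on normal changes, and on the SD implied by the cited effect sizes. If r is about 0.7 or higher and there is no shared fall, the 20% rule seldom misfires on systolic pressure. With a shared fall of 2.5 mmHg it is nearly always met at r = 0.7, and close to half the time at 0.8. Fewer than 500 analysed per arm would pull the probabilities away from 0% and 100% without changing the pattern.

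The mean rule is not prone to chance success, but a fall common to all arms can satisfy it if it is read within one arm. Whether the primary outcome alone should decide every claim, or whether secondary outcomes should be tested in a fixed order, is a design choice that the documents do not settle.

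**What to change.** In Research questions and hypotheses:

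1. Base any blood pressure conclusion on the baseline-adjusted mean difference from control already planned under Intervention effectiveness.
2. Report the share falling by more than 10 mmHg in each arm, and its difference from control with a 95% confidence interval, without a success verdict.
3. State that blood pressure and sport results are secondary, supportive findings, and that they do not make an intervention successful when the primary activity comparison is negative.

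The cost is wording only, with no new patients, visits or data. What is given up is a success claim that rests only on the responder share. The comparison with control can carry the conclusion at the plan's own threshold. A 2.5 mmHg difference is 2.5/14.1 = 0.178 SD, and 0.178 × √(500/2) = 2.81, so power at two-sided 5% is Φ(2.81 − 1.96) = 80% with 500 analysed per arm, before any gain from baseline adjustment.

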### Measures

PA will be assessed via an online questionnaire using the short-form version of the International Physical Activity Questionnaire
[29], which is a well validated measure of physical activity in a number of domains and permits the calculation of MET per minute values for activities in each domain, including leisure and sporting activity
[30]. As recent research has shown that the International Physical Activity Questionnaire can overestimate activity in sedentary individuals we will use a second validated self-report measure, the Self-Report Walking and Exercise Tables
[31] that also permits the estimation of MET minutes. We will include additional items to tap the types of sporting activity people do.

Participants will complete the GPPAQ screening tool at the beginning and end of the study for inclusion on their patient records.

Health indicators will include measures of height and weight (body mass index (BMI)), waist and hip circumference, and blood pressure. These measures will be assessed by the exercise professional at the beginning, middle and end of the 12-week exercise programme. They will be collected again at the end of the 12-month period on visiting their GP surgery. Patients will be asked to consent to the collection of their most recent blood sugar, cholesterol/high-density lipoprotein ratio and indications of whether they are receiving treatment for high blood pressure. We will ask for access to medical records to assess whether they have chronic kidney disease, diabetes, rheumatoid arthritis or atrial fibrillation. These indicators are required for the QRisk2 calculations. To assess safety we will also monitor well-being during the period of the exercise programmes. Blood pressure measurements will be taken by the research team and/or by specially trained exercise professionals using Omron M6W blood pressure monitors (Omron Health Care Co. Ltd, [name]).

General health will be assessed with the RAND SF36
[32] along with short measures of drinking (the AUDIT
[33]) and smoking behaviour (The Fagerstrom Test
[34]). These will be assessed at baseline and at 12 month follow-up.

Intervention exposure will be assessed by attendance at the exercise programme sessions. Web-tool usage will be assessed by number and duration of logins over the study period.

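### The between-arm comparison of falls above 10 mmHg uses an unadjusted chi-square test although baseline blood pressure is collected: valid, but it gives up some precision

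*Protocol article*

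**What the plan says.** Under Research questions and hypotheses the article introduces the responder outcome: "We will assess the proportion of the sample reducing their blood pressure by more than 10 mmHg". It attaches a rule to each arm, under which an intervention is "regarded as a success if more than 20% of the members of that study arm achieve a reduction greater than this". The target for the mean is separate: the interventions should "lead to an average decrease in blood pressure of 2.5 mmHg".

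Under Intervention effectiveness the responder shares are compared between arms by a named test: "Differences between arms in the proportions achieving more than 10 mmHg reductions in blood pressure will be assessed using chi-square tests". No covariate is mentioned. The same paragraph analyses the primary outcome by t-tests and by analysis of covariance with "baseline activity scores as the covariate", and extends similar analyses to the secondary outcomes. Mean blood pressure is therefore already due a baseline-adjusted analysis.

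Under Measures, blood pressure is among the health indicators: "These measures will be assessed by the exercise professional at the beginning, middle and end of the 12-week exercise programme". For follow-up, "They will be collected again at the end of the 12-month period on visiting their GP surgery". The baseline value is therefore available. Randomisation is in blocks, and no stratification by blood pressure is stated.

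**The concern.** A responder defined by change from baseline depends on where the participant started. Entrants run from high-normal pressure to diagnosed hypertension. A high first reading tends to be followed by a lower one whatever the treatment, so participants who start high are more likely to record a fall above 10 mmHg.

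The plan applies baseline adjustment to the continuous outcomes and names a test without it for this comparison. Two things follow. The test has less power than the same data could give. And if the arms happen to differ in starting pressure, part of that difference passes into the reported difference in response, with nothing in the analysis to remove it.

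**Working it through.** **The plan's own figure.** The article gives no power for the responder comparison. Its one power statement concerns means: "an effect size of 0.125 can be assumed for comparing means of MET-minutes per week and mmHg", with 500 per arm said to give 80% power, two-sided 5%. Check: 0.125 × √(500/2) = 1.976; 1.976 − 1.960 = 0.016; Φ(0.016) = 50.7%. The 80% is not reproduced. That is a separate matter and nothing below depends on it.

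**Inputs from the article.** 500 per arm; two-sided 5%; d = 0.125; 2.5 mmHg; systolic effect of 3.8 mmHg equated with an SMD of 0.27.

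**Assumptions.**
- Systolic SD = 3.8/0.27 = 14.1 mmHg, back-calculated from a meta-analysis of other trials. The planned effect is then 0.125 × 14.1 = 1.76 mmHg.
- Baseline and follow-up are bivariate normal with correlation r = 0.4, 0.6 or 0.8 (not given in the article).
- A common fall of 2 mmHg in both arms (assumed).
- The 10 mmHg rule is applied to systolic pressure; the article does not say which pressure it means.
- No dropout is applied, since no rate is given.

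**How far baseline predicts response.** The fall has SD 14.1 × √(2(1 − r)) and correlates √((1 − r)/2) with baseline: 0.55, 0.45 and 0.32 for r = 0.4, 0.6 and 0.8. After dichotomising at 10 mmHg, the simulated correlations with response are about 0.42, 0.34 and 0.22. The link is built in; its strength depends on r.

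**Response rates.** P(fall > 10) = 1 − Φ((10 − mean fall)/SD of fall). For r = 0.6 the SD of the fall is 12.6. Control: 1 − Φ(8/12.6) = 26%. With a further 2.5 mmHg: 1 − Φ(5.5/12.6) = 33%. The simulated true differences at 2.5 mmHg are 5.8, 6.9 and 8.5 points for r = 0.4, 0.6 and 0.8.

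**Power.** Simulation, 3,000 trials per setting: chi-square against logistic regression on arm and baseline pressure.

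| r | True effect | Chi-square | Adjusted logistic | Gain (points) |
|---|---|---|---|---|
| 0.4 | 1.76 mmHg | 27.0% | 32.0% | 5.0 |
| 0.6 | 1.76 mmHg | 37.4% | 42.4% | 5.0 |
| 0.8 | 1.76 mmHg | 58.2% | 60.6% | 2.4 |
| 0.4 | 2.5 mmHg | 49.9% | 58.3% | 8.4 |
| 0.6 | 2.5 mmHg | 66.2% | 72.1% | 5.9 |
| 0.8 | 2.5 mmHg | 89.9% | 91.0% | 1.1 |

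With no effect, rejection rates were 4.7-5.3% for chi-square and 4.3-5.4% for the adjusted model. The variance of the standardised risk difference was 0.80-0.83 (r = 0.4), 0.86-0.88 (r = 0.6) and 0.95-0.96 (r = 0.8) of the unadjusted variance. A further simulation over r = 0.5 to 0.7 gave gains of 3.9 to 6.5 points at the same two effects.

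**Chance imbalance.** The SD of the difference in mean baseline is 14.1 × √(2/500) = 0.89 mmHg, so the 95% limit is 1.96 × 0.89 = 1.74 mmHg. With no treatment effect, each 1 mmHg of imbalance moved the unadjusted risk difference by 1.34, 1.06 and 0.58 points (r = 0.4, 0.6, 0.8). At the limit that is 1.34 × 1.74 = 2.3, 1.06 × 1.74 = 1.8 and 0.58 × 1.74 = 1.0 points.

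**The case against.** The strongest reply is that nothing here is an error. A chi-square test of two randomised proportions holds its level, and chance imbalance is already part of the sampling variation it allows for. That stands. A reader might infer bias from the imbalance figures. There is none on average over randomisation, and the 1 to 2.3 point shift applies only to an allocation at the 95% limit.

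A second reply is that blood pressure is secondary, and mean blood pressure already gets a baseline-adjusted analysis that is far more powerful: 86% to 99.7% at 2.5 mmHg in the same simulations. That also stands. It would be tempting to set those figures against the chi-square power and call the gap the loss. Most of that gap comes from dichotomising, and the analysis that avoids dichotomising is already in the plan. Adjusting the responder comparison recovers only the 1 to 8 points in the table.

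Third, a reader might infer that the unadjusted test undermines the declared success criterion. It does not. That rule sets an arm's observed share against a fixed 20%; neither the chi-square test nor a logistic model decides it.

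Fourth, 2.5 mmHg is stated as an average decrease under the interventions, not as a difference from control. The between-arm effect the article plans for is d = 0.125, and there power is low with either test if r is moderate. Adjustment does not rescue the comparison. The 2.5 mmHg rows are illustrative.

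Finally, an article may leave covariates to a fuller plan. Here, however, the test is named, and it has no place for a covariate.

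**Conclusion.** The point holds as one of efficiency. The article fixes an unadjusted test for a change-based responder outcome while collecting the baseline value that bears on it. Adjustment helped at both effect sizes and every correlation in the table, by about 1 to 8 power points, most when the baseline/follow-up correlation is low and hardly at all at 0.8. It also removes chance baseline imbalance that could otherwise move the estimate by 1 to 2.3 points at the 95% limit, against true differences of about 6 to 8.5 points at 2.5 mmHg.

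These sizes rest on a back-calculated SD, an assumed correlation, an assumed common fall and normality. The direction does not depend on their exact values. The documents do not support calling the chi-square test invalid or biased. Priority is low to moderate.

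**What to change.** Under Intervention effectiveness, replace the chi-square test with logistic regression of response (fall above 10 mmHg) on study arm and baseline blood pressure as a continuous covariate. Report the standardised risk difference with its 95% CI, so that the result remains a comparison of proportions and is not left as a conditional odds ratio. Show the crude share in each arm beside it, since the separate 20% rule is read from those shares and stays as it is.

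The cost is one line of analysis wording. No new data, visits or participants are needed.
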